### Statistical analysis

All variables will be checked for normality using both statistical and graphical methods. Results will be presented as frequencies and proportions with 95% confidence intervals for categorical variables and mean (standard deviation) or median (range) for continuous variables. A descriptive analysis of the participants characteristics will be performed as soon as the baseline assessments are completed. This cross-sectional analysis will show the comparability of IG and CG and the need for adjustment when between group comparisons are done.

General Lineal Models will be used to examine the training effects [time (pre-post 9-month intervention) x group interaction] on the primary and secondary outcomes. Change in bone outcomes will be used as age and sex-adjusted z-scores. The baseline level of each outcome variable will be entered as covariate. Effect sizes will be reported. Multiple imputation methods and sensitivity analysis (i.e. propensity score) will be performed to handle missing data and appreciate the potential influence of missing responses. Finally, in the event of possible dropouts, a statistical analysis will be carried out by protocol and intention to treat.

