### Randomization and blinding

Randomization to an intervention group (online exercise programme, IG) or control group (no treatment, CG) will be performed by an external partner ([name]) who is independent of the participant recruitment and enrolment process, stratified by age and sex. Each participant will be provided a uniform (0, 1) random number using SAS software, version 9.1 (SAS Institute Inc), within their respective age and sex group. Assignments will be blinded to the assessors until all tests are completed. For feasibility reasons, the study will probably be conducted in two waves of 58 children at most.

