### Sample size

We have used femoral neck aBMD as the outcome to calculate the sample size, since it is a key variable in the diagnosis of osteoporosis. Since the study will include children and adolescents (6–18 years), the sample size has been calculated taking into account that sub-group analysis by age groups (6 to 11 years and 12 to 18 years) may be required. Based on an expected effect size of 0.25 for the change in femoral neck aBMD, an α level of 0.05 and a power of 80%, a minimum of 116 participants will be required (IG = 58 and CG = 58). This includes a 20% extra for occasional losses and refusals and 10% for multivariable analyses. Calculations have been obtained using G*Power (v.3.1.9.2) with analysis of variance: repeated measures (within-between interactions) for 2 groups (between factors) and 2 time points (pre, post, within factors). A correlation between measures of 0.7 has been assumed, which is achievable when measuring bone outcomes [16].

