### Secondary outcomes

#### Anthropometric measurement, body composition and somatic maturation

Body mass (kg) will be measured with an electronic scale (SECA 861, Hamburg, Germany) with an accuracy of 100 g. Height (cm) will be measured by using a precision stadiometer (SECA 225, Hamburg, Germany) to the nearest 0.1 cm. Body mass index (BMI) will be calculated as body mass (kg)/height (m^2^), and the participants will be classified into BMI categories according to sex- and age-specific cut offs [80].

In addition to DXA measurements, a bioimpedance scale (Tanita BC-418 MA; Amsterdam, The Netherlands; range: 2–200 kg; precision: 0.1 kg; body fat percentage increments: 0.1%) will estimate the percentage of body fat of the participants. The assessment will be carried out in fasting state according to the manufacturer’s instructions. Despite the measured error, bioelectrical impedance analysis will be used to assess body fat as it is considered a practical method in addition to DXA [81].

Somatic maturation will be assessed using the prediction of years from peak height velocity using validated algorithms for children [82].

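### The observed baseline comparison decides which covariates are adjusted for, and the randomisation strata (age and sex) are not among the fixed model terms

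*Protocol article*

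**What the plan says.** All of this is in the protocol article.

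- **Statistical analysis, rule for adjustment.** "A descriptive analysis of the participants characteristics will be performed as soon as the baseline assessments are completed". The next sentence gives its purpose: "This cross-sectional analysis will show the comparability of IG and CG and the need for adjustment when between group comparisons are done". No candidate covariates are listed, and nothing says how large a difference would call for adjustment.
- **Statistical analysis, model.** "General Lineal Models will be used to examine the training effects", through a time-by-group term, on primary and secondary outcomes alike. One covariate is fixed: "The baseline level of each outcome variable will be entered as covariate".
- **Statistical analysis, scale.** "Change in bone outcomes will be used as age and sex-adjusted z-scores". This covers bone outcomes only.
- **Randomization and blinding.** Allocation is "stratified by age and sex". Neither factor is named as a model term.
- **Anthropometric measurement, body composition and somatic maturation.** "Somatic maturation will be assessed using the prediction of years from peak height velocity". Maturity is therefore collected, but it has no stated role in the model.

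**The concern.** Randomised arms differ at baseline only by chance, so the size of an observed difference says little about whether a variable belongs in the model. What matters is how strongly the variable predicts the outcome. A rule driven by imbalance can leave out a strong predictor that happens to balance and admit a weak one that does not. With no list and no threshold, it also leaves several adjusted models available, and nothing in the text fixes which of them is the analysis.

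The strata raise a related matter. Stratifying on age and sex removes their contribution to the variability of the treatment estimate. A model that ignores them still counts that contribution in the residual, so it reports a standard error that is too large. Ages run from 6 to 18 years, and shuttle run, handgrip, long jump, lean mass and activity are not put on age- and sex-adjusted scales. What is at stake is a fixed analysis for every outcome and honest standard errors, mainly for the secondary outcomes.

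**Working it through.** The plan gives no figure on this point, so there is none to reproduce. The check is how much the two features could matter.

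**Inputs from the protocol article.** Total sample 116, allocated 1:1; correlation between measures 0.7; allowances of 20% for losses and 10% for multivariable analyses (Sample size); strata age and sex (Randomization and blinding).

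**Assumptions not in the documents.**
- Evaluable n = 116/(1.2 × 1.1) = 116/1.32 = 87.9, taken as 88.
- Four strata (two age groups by sex), with 1:1 balance inside each.
- Six candidate baseline covariates.
- Share R² of the variance left after baseline adjustment that the strata explain: 0%, 10% or 20%.
- For power, a true effect of 0.4 baseline SD.

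**Standard error by formula, in baseline SD units.**
- Baseline value only: √(1 − 0.7²) × √(4/88) = 0.714 × 0.213 = 0.152.
- With strata added, multiply by √(1 − R²). For R² = 0% the result is 0.152. For 10% it is 0.152 × 0.949 = 0.144. For 20% it is 0.152 × 0.894 = 0.136.

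**Simulation of the same model (2,000 to 3,000 trials per scenario).**

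| R² of strata | Reported SE, without → with strata | True spread of estimate, without → with | Type I error without strata | Power, without → with |
|---|---|---|---|---|
| 0% | 0.153 → 0.153 | no change | 4.7% to 5.5% | no gain |
| 10% | 0.153 → 0.145 | 0.1435 → 0.1433 | 3.5% | 73% → 77% |
| 20% | 0.153 → 0.137 | 0.1388 → 0.1378 | 3.0% | 77% → 83% |

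The reported SE falls by 1 − 0.145/0.153 = 5% and by 1 − 0.137/0.153 = 10%. The true spread hardly moves, because stratification has already balanced the strata. The fault is an overstated SE, and the test is conservative.

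The type I error agrees with a normal approximation. The effective critical value is 1.96/0.949 = 2.07 at 10%, a two-sided error of about 3.9%. At 20% it is 1.96/0.894 = 2.19, about 2.8%.

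**Choosing covariates from the observed comparison.** Two readings of the rule were simulated with no true effect:
- Mechanical rule (adjust for any candidate with a baseline p-value below 0.05): type I error 2.7% to 5.2%, so no inflation.
- Free choice among the adjusted models by the smallest p-value for treatment: type I error 6.4% to 12.3%.

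The text describes neither. It does not prescribe the second, but because nothing is fixed it does not exclude it.

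**Which outcomes are affected.** Bone outcomes are z-scores adjusted for age and sex, so both strata already enter through the scale, and the 0% row may apply to them. Other outcomes have no such protection. Their baseline value carries part of the age and sex effect, so the R² that counts is what age and sex predict beyond baseline, such as differences in growth over nine months. The documents give no value for it.

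**The case against.** **The primary outcome is largely protected.** Bone health is primary and is analysed on age- and sex-adjusted z-scores with the baseline value as a fixed covariate. A reader might infer that the primary test is data-driven and imprecise. The documents do not support that: the core of the model is fixed, and adding age and sex may gain nothing. This objection stands.

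**The look comes before the outcomes.** The baseline comparison is planned once baseline assessments are complete. Covariates settled then would be chosen blind to the 9-month results, and a mechanical rule did not inflate the error rate. A reader might infer an inflated type I error from the sentence alone. That would need a choice made on results, which the text does not describe, and omitting the strata pushes the error rate down. This mostly stands. The limit is that Randomization and blinding expects two waves as likely, and the article does not say that all baseline assessments will finish before the first wave has 9-month data.

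**This is a condensed article.** A full covariate list is commonly left to an analysis plan, naming one covariate does not exclude others, and the 10% allowance for multivariable analyses shows that adjustment is foreseen. For the missing list alone this would be a full answer. It does not answer the rule: the article states that the comparison of arms will show what needs adjustment, and an analysis plan could only overrule that.

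**The precision figures rest on assumption.** The 10% to 20% share is assumed, and 0% is quite possible for the bone z-scores. This stands.

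**Conclusion.** The point holds in a limited form. The article states a balance-driven rule for adjustment, with no candidates and no threshold, and fixes only the baseline value although it stratifies on age and sex. That is a poor basis for covariate choice and leaves the adjusted model open.

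- For outcomes without age- and sex-adjusted scaling, omitting the strata makes standard errors too large and tests conservative. The amount depends on how far age and sex predict the outcome beyond its baseline.
- For the bone z-scores the gain may be nil. It is about 5% to 10% in reported SE only if the strata still explain 10% to 20% of residual variance.
- These figures assume 88 evaluable participants, a correlation of 0.7 and balance within strata.

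A reader might turn the 10% to 20% into an equivalent of 11% to 25% more participants (1/0.90 = 1.11; 1/0.80 = 1.25). That should not be claimed for the primary test: it leaves out 0% and reflects the reported SE, while the true spread of the estimate hardly changed.

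**What to change.** Delete the sentence that lets the baseline comparison show what needs adjustment, and keep the baseline table as description only. In its place, state the model for every outcome, for example:

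> Each outcome will be analysed with treatment group, the baseline value of that outcome, and the randomisation strata (age group and sex). Any further prognostic covariate will be named, with its form, before outcome data are seen. Observed differences between the arms at baseline will not alter the model.

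Baseline maturity offset is a natural candidate, since it is already collected. If it is wanted, it should be named now, using the baseline value only.

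The bone outcomes can carry the same strata terms for uniformity, even if the z-scores leave them little to explain. The cost is wording and a few degrees of freedom. No change to data collection or sample size is needed.

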## Background

Owing to major advances in cancer screening and treatment over the last 30 years, cancer survival has improved dramatically. In Europe, the paediatric cancer incidence increases annually by 0.54% in children (0–14 years) and by 0.96% in adolescents (15–19 years), although it seems that the incidence in adolescents is decelerating [1]. Nevertheless, the 5-year survival rate is now at 77.9% for children and 79% for adolescents and young adults (20–39 years) [2, 3]. Unfortunately, the treatment of paediatric cancer by means of radiation, chemotherapy and/or surgery is associated with various late effects (e.g. impaired growth, musculoskeletal sequelae, cardiopulmonary compromise and secondary malignancy) [4–6], predisposing paediatric cancer survivors to disabling conditions [4]. Furthermore, paediatric cancer treatment has been documented to have an effect on emotional well-being and quality of life, with survivors reporting anxiety, depression and post-traumatic stress [7, 8].

Paediatric cancer is a life-threatening condition that also occurs during the period of bone development and strengthening. Gonadal failure following to pelvic radiation or gonadotoxic chemotherapy and hypothalamic pituitary dysfunction by means of cranial radiation can adversely affect areal bone mineral density (aBMD), increasing osteoporosis risk later in life [9, 10]. In addition, direct radiation to bone not only causes hypovascularity but has a direct cytotoxic effect on the epiphyseal chondrocytes [11]. Observational studies have found low aBMD during and after cancer treatment to be associated with increased fracture risk (80% increase for every 1 SD reduction in lumbar spine aBMD Z-score) [12–15], which can lead to a higher risk of osteopenia and osteoporosis in adulthood and finally, disability [16, 17]. Moreover, data from a review showed that up to 68% of paediatric cancer survivors presented moderate-to-severe aBMD deficits (Z-score < − 1), while up to 46% had severe aBMD deficits (Z-score < − 2) [18].

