### Primary outcome: bone health

#### Dual-energy X-ray Absorptiometry (DXA)

A DXA (Hologic Series Discovery QDR, Bedford, MA, USA) will be used throughout the study to obtain BMC (g) and aBMD (g/cm^2^) for the hip, lumbar spine and total body less head. Furthermore, lean soft tissue mass (g), fat mass (kg) and body fat percentage (%) for the whole body will be obtained from total body scans. APEX software (version 4.0.2) will be used to analyse the scans following the recommendations for children and adolescents [70]. Equipment calibration, participant setting and scan analyses will be performed by the same researcher. DXA uses a minimal radiation (i.e. spending a day outside in the sunshine) and the effective dose for the scans in children has been set in 3–6 μSv [71].

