## Discussion

The iBoneFIT study will examine the effect of an online RCT exercise programme on bone health in paediatric cancer survivors aged 6–18 years old. In addition, it will follow up the participants 4 months after the intervention to examine whether the effects remain. Finally, the iBoneFIT study will investigate whether the intervention affects body composition, physical fitness, physical activity, quality of life and mental health of paediatric cancer survivors.

Previous evidence shows a higher risk of delayed bone development, diminished muscle functioning, disability and compromised fundamental movement skill acquisition in children who have completed cancer treatment [79]. These side effects can also reduce motivation to be physically active and aggravate chronic health conditions in the short and long terms [100]. A recent longitudinal review showed that higher levels of muscular fitness in childhood and adolescent were associated with higher aBMD later in life [101]. Moreover, jumping interventions have shown improvements in both muscular fitness and bone health [38, 39, 102]. In this regard, Vlachopoulos et al. [39] reported an increase in physical fitness (3.7–7.9%) and BMC at TBLH and legs (4.2–12.7%) in non-osteogenic sports. Additionally, Vlachopoulos et al. [38] showed that a 9-month plyometric training improved LS BMC (4.6%) and femoral neck BMC (6–9.8%) in non-osteogenic sports. Another study carried out by Mackelvie et al. [102] suggested that jump training was associated with increases in femoral neck, lumbar spine and total body aBMD (~ 2%) in prepubertal boys and may delay the onset of osteoporosis later in life. The Exercise Guidelines for Cancer Survivors recommend avoiding movements that place excessively high load on fragile skeletal sites [43]. Thus, our intervention aims to improve muscular strength before implementing mechanical loading through jumping exercises.

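### Bone outcomes are standardised for age and sex only; baseline height and maturity, already measured, should be prespecified covariates, with a height-adjusted sensitivity analysis

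*Protocol article*

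**What the plan says.** The Statistical analysis section fixes the scale of the bone endpoints: "Change in bone outcomes will be used as age and sex-adjusted z-scores". It names one covariate: "The baseline level of each outcome variable will be entered as covariate". Beyond that, a descriptive baseline analysis is to show "the comparability of IG and CG and the need for adjustment when between group comparisons are done"; no variable is named for that step.

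The DXA section says the scans will be used "to obtain BMC (g) and aBMD (g/cm^2^) for the hip, lumbar spine and total body less head". The hip structural analysis adds cross-sectional area (mm²), section modulus (mm³) and moment of inertia (mm⁴). Femoral neck areal density is the outcome behind the sample size.

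The Background gives as examples of late effects "impaired growth, musculoskeletal sequelae, cardiopulmonary compromise and secondary malignancy". It also describes gonadal failure and hypothalamic pituitary dysfunction after treatment.

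Under the anthropometry heading, "Height (cm) will be measured by using a precision stadiometer (SECA 225, Hamburg, Germany) to the nearest 0.1 cm", and somatic maturation is assessed as predicted years from peak height velocity. The protocol links neither to a bone z-score or to a bone model.

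**The concern.** Areal density is mineral per projected area. At the same volumetric density it rises with bone depth, and so with size. Mineral content and the hip geometry measures rise more steeply still. Standardising for age and sex removes the size differences that go with age and sex in the reference population. It leaves those that arise because a child is short, or early or late in maturing, for that age. The protocol itself says that growth can be impaired in this population, so this remainder may not be small.

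Three things are at stake. Variation in size and maturity stays in the residual and widens the confidence interval. A chance difference between arms in size or maturity moves the estimate. And if an effect is found, the planned analysis cannot say whether it is mineral accrual at a given size or is tied to growth.

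**Working it through.** The plan gives no figure on this point to reproduce. The inputs from the protocol are 58 children per arm (116 in all), the units of the outcomes, and the assumed correlation of 0.7 between repeated measures. Every correlation with growth below is an assumption, because the protocol gives none.

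**1. Dependence on size.** Take two bones of the same shape and volumetric density, one scaled by 0.9 in every dimension (simple geometry):

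| Measure | Scales as | Ratio | Lower by |
|---|---|---|---|
| Areal density | length¹ | 0.900 | 10% |
| Mineral content, section modulus | length³ | 0.729 | 27% |
| Moment of inertia | length⁴ | 0.656 | 34% |

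This concerns the score of a single child. It is not an error in the comparison of arms.

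**2. Precision.** If covariates have correlation r with the outcome, given what is already in the model, the residual variance is multiplied by 1 − r².

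- r = 0.3: 1 − 0.09 = 0.91, so 9% is removed. 116 / 0.91 ≈ 127.
- r = 0.5: 1 − 0.25 = 0.75, so 25% is removed. 116 / 0.75 ≈ 155.

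So 116 children would carry the information of about 127 to 155. Here r must be the correlation that remains after age, sex and the baseline outcome. With a pre-post correlation of 0.7, the baseline value alone may account for about 0.7² = 49% of the variance of the later value, and stable differences in size are part of that.

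**3. Chance imbalance.** For a characteristic with SD 1, the standard error of the difference between arm means is √(2/58) = 0.186. A difference of at least 0.2 SD in either direction has z = 0.2 / 0.186 = 1.08, a probability of about 28%. If the characteristic correlates r with the outcome, such an imbalance moves the estimate by r × 0.2: 0.06 SD at r = 0.3 and 0.10 SD at r = 0.5. That is about a third to a half of the standard error of the arm contrast (also 0.186 when the outcome has SD 1).

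**4. Is the contrast biased?** In a simulation with 58 per arm and 4,000 runs per setting, change in bone z-score had SD 1 and correlation r with growth, and there was no true effect apart from growth.

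| r | Systematic arm difference in growth | Unadjusted: mean estimate, type I error | Adjusted for growth: mean estimate, type I error |
|---|---|---|---|
| 0.3 | none | −0.002, 4.4% | −0.002, 4.6% |
| 0.5 | none | −0.002, 4.5% | 0.001, 5.2% |
| 0.7 | none | 0.001, 5.3% | 0.001, 4.8% |
| 0.3 | 0.2 SD | 0.059, 6.3% | −0.001, 5.0% |
| 0.5 | 0.2 SD | 0.102, 7.9% | 0.000, 4.9% |
| 0.7 | 0.2 SD | 0.147, 12.1% | 0.002, 4.6% |

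Without a systematic difference in growth, the planned contrast is unbiased and its error rate is nominal. It shifts, by about r × 0.2, only when growth itself differs by arm.

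**The case against.** The strongest reply is randomisation. Allocation is 1:1 and stratified by age and sex, and the baseline outcome is in the model. Pre-existing short stature is therefore balanced in expectation and partly absorbed by the baseline value, and the standard error already allows for chance imbalance. This stands, and it limits the point to precision and interpretation.

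A reader might go further and infer that the trial will report differences in growth as a treatment effect on bone. The documents do not support that: nothing in them says that growth over the nine months differs by arm. Nor can chance imbalance in growth plausibly produce an effect of the size that the Discussion cites, where "jump training was associated with increases in femoral neck, lumbar spine and total body aBMD (~ 2%) in prepubertal boys". By simple geometry, one child who grows 2% more than age peers gains about 2% in areal density, but the cited figure is a group effect. If excess growth had an SD of 1% to 2% between children (assumed), the standard error of the arm difference would be 0.19% to 0.37%, and a 2% imbalance would lie 5 to 11 standard errors out. The Z-score cut-offs in the Background are likewise no ground for concern: they come from a review and are neither eligibility criteria nor endpoints.

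It can also be said that the primary outcome includes volumetric 3D-DXA measures and trabecular bone score. That is true, but the first covers the proximal femur and the second the lumbar spine, neither is given priority, and neither corrects areal density or mineral content at the hip, spine or total body.

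Finally, the sample size allows 10% for multivariable analyses, the baseline comparison may lead to adjustment, and a covariate list may stand in an analysis plan not shown. Further covariates are thus foreseen, and the article does not prove that height and maturity will be left out. But the adjustment step it does state turns on observed imbalance. Covariates earn their place by how well they predict the outcome, whether or not the arms happen to differ, and a baseline comparison says nothing about growth afterwards.

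**Conclusion.** The point holds as one of precision and interpretation. The stated metric handles size and maturity only through age, sex and the baseline outcome, in a population whose growth the protocol describes as liable to impairment, while better measures are already being collected.

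The possible gain is 9% to 25% of the residual variance. It rests on an assumed correlation of 0.3 to 0.5 after age, sex and baseline outcome are accounted for. Covariates measured at baseline predict only part of later growth, so the lower end may be nearer the truth. Bias in the arm contrast would need growth to differ by arm, which the documents neither state nor exclude.

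**What to change.** In the Statistical analysis section:

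1. Prespecify baseline height and baseline years from peak height velocity as covariates, with the baseline outcome, age and sex, in all bone-outcome models, whatever the observed baseline imbalance. Being measured before the intervention, they leave the treatment comparison intact. If they are strongly correlated with age or with each other, their own coefficients suffer, not the treatment contrast.
2. Keep the age- and sex-adjusted z-scores, and beside them name one sensitivity analysis for areal density and mineral content: height-adjusted z-scores, with the reference stated, or models adjusted for change in height. State that height at later visits is measured after randomisation, so this analysis targets size-adjusted density, a different question from the main one.

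The cost is a few degrees of freedom (four at most, of about 113 with 116 children) and one extra analysis. No new data are needed. Settling it before the outcome data are seen also avoids a later choice between metrics.

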### Participant adherence and compliance

Participants will be allowed to withdraw at any time; nevertheless, several strategies will be used for adherence and compliance with the intervention. The minimum compliance allowed at each phase of the intervention will be 50% but the overall compliance after 9 months will have to reach 70%. A lack of compliance (< 50%) without justified reasons in the first phase of the intervention will result in the participant being invited to drop out from the study. This 70% adherence rate means completing 95 sessions of 136. If a participant has not completed 70% of the intervention by the end of the 9 months but can reach 70% within two additional weeks, the exercise programme will be extended for them. Compliance with the intervention will be monitored using a diary and it will be sent to the research staff on a monthly basis (Item 5). Parental involvement will be requested for this matter.

Participants and their parents are verbally motivated to participate in the intervention and to attend to all the assessments. Children who complete successfully the intervention will get a certificate of achievement. Children are the key part of this study and they deserve acknowledgements for their positive attitude and willingness (and their family) to participate in this study.

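### The one sensitivity analysis named for missing data shares multiple imputation's missing-at-random assumption, while the exit rule can produce compliance-related loss in the exercise arm only

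*Protocol article*

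**What the plan says.** Under Statistical analysis, the protocol article states: "Multiple imputation methods and sensitivity analysis (i.e. propensity score) will be performed to handle missing data", and also to gauge how far missing responses could matter. It names no other sensitivity analysis for missing data. It does not state a missingness assumption, list the variables in the imputation or propensity model, or say how the propensity score would be used. It adds that "in the event of possible dropouts, a statistical analysis will be carried out by protocol and intention to treat".

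Under Participant adherence and compliance, the floor is 50% in each phase and 70% overall. Unjustified compliance below 50% in the first phase "will result in the participant being invited to drop out from the study". The text attaches no such consequence to low compliance in phases 2 and 3. It also says: "Compliance with the intervention will be monitored using a diary and it will be sent to the research staff on a monthly basis".

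Under Control group, children in that arm receive calcium and vitamin D information and have no sessions until the study is over. The exit rule can therefore act in the exercise arm only.

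**The concern.** A sensitivity analysis for missing data is useful when it relaxes the assumption that the main analysis depends on. Standard multiple imputation and weighting by a response propensity depend on the same one: given the variables in the model, children without a scan would have had outcomes like those of children with one. If that fails, both methods move in the same direction, and their agreement says nothing about whether it holds.

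The exit rule gives a specific reason to doubt it. A child who leaves under the rule has trained little, and the text does not say that such a child is still scanned at T1. If only arm and baseline enter the models, that child is in effect credited with the gain of children who went on to the jumping phases. At stake is an intention-to-treat effect on bone that may be too large, next to a check that appears to confirm it.

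**Working it through.** **1. Check the plan's own session figures.** From Table 3, sessions = 4 weeks × (4+4+3+4+4+3+4+4+4) = 4 × 34 = 136, as stated. Seventy per cent is 0.70 × 136 = 95.2, which agrees with the stated 95. Jumps are 2360 (phase 2) + 2936 (phase 3) = 5296, as stated.

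**2. Exposure of a child who leaves under the rule.** Phase 1 has 8 weeks × 4 = 32 sessions. Below 50% means fewer than 16 sessions, and 16/136 = 11.8% of the programme. Phase 1 consists of squats, and the jumps in Table 3 start in week 9. A child who leaves by the end of phase 1 has done none of those 5296 jumps (the warm-up may contain some jump patterns). Leaving by that point is an assumption, because the exact time of the invitation is not given.

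**3. Bias formula.** Let p be the share of the exercise arm that leaves without a T1 scan, d the gain over control in those who stay, and e the gain in those who leave. Suppose also that leavers and stayers with the same baseline would do equally well without exercise.

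- True intention-to-treat effect: (1−p)d + pe
- Missing-at-random estimate on arm and baseline: d
- Overstatement: p(d−e). With e = 0 this is p/(1−p) of the true effect. With e = d/2 it is (p/2)/(1−p/2).

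The documents give neither p nor e, so both are assumed:

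| p (assumed) | leavers gain nothing | leavers keep half |
|---|---|---|
| 10% | 0.10/0.90 = 11% | 0.05/0.95 = 5% |
| 20% | 0.20/0.80 = 25% | 0.10/0.90 = 11% |
| 30% | 0.30/0.70 = 43% | 0.15/0.85 = 18% |

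**4. Do the two named methods move together?** A simulation used 58 per arm and a correlation of 0.7 (both from Sample size). It assumed 5% random loss in each arm, a gain of 0.5 SD in stayers and none in leavers. Imputation and response-propensity weighting both used arm and baseline.

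| p | full-data effect (SD) | multiple imputation | propensity weighting |
|---|---|---|---|
| 10% | 0.455 | 0.505 | 0.505 |
| 20% | 0.404 | 0.503 | 0.502 |
| 30% | 0.348 | 0.499 | 0.499 |

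The two methods agree to within 0.001 SD, and both miss the full-data effect by about p × d.

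**5. Does the diary help?** A second simulation drew individual compliance at random, made the gain proportional to it (0.5 SD at 70%), and let every exercise-arm child below 50% leave (about 23% of the arm). The full-data effect was 0.461. Imputation without compliance gave 0.524, and with compliance 0.462. When half of such children left (about 12% of the arm), the figures were 0.464, 0.492 and 0.465. The recovery depends on the linear relation. When every child below 50% leaves, no outcomes are seen in that range and the model extrapolates. The simulation also used one compliance value for the whole programme, whereas a child who leaves early has a diary for phase 1 only.

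**6. What control-based imputation does.** It gives leavers the control-arm outcome, so its estimate is (1−p)d. With p = 20%, d = 0.50 and e = 0, that is 0.40, the true value by construction. If leavers keep half the gain, the truth is 0.90d and the estimate 0.80d, an understatement of 0.10/0.90 = 11%. For any e between 0 and d, the missing-at-random and control-based estimates bracket the truth under the assumptions in step 3.

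**The case against.** Several points on the other side stand.

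- A reader might infer that the plan removes poor compliers. It does not. They are invited to leave, may decline, and the rule covers only unjustified low compliance in phase 1. Children with justified reasons, or who fall short later, can still be scanned, so the observed exercise arm is not made up purely of good compliers. That those who leave will lack a T1 scan is likely but not stated.
- A reader might infer that the named check can never detect the bias. That is too strong. Compliance is recorded before exit, so loss caused by the rule could be missing at random given the diary. Step 5 shows that this can work under favourable conditions. It is only a partial rescue: a low complier who stays goes on to the jumping phases and one who leaves does not, so stayers are poor donors even at equal phase 1 compliance.
- The article does not state missing at random; it is the default of the named methods. Nor does it say that the propensity score is a response-propensity weight. An analysis plan that is not shown may specify more. The point therefore does not rest on the absence of model details. It rests on the published text naming one check, for the stated purpose of gauging the influence of missing responses, that in its usual form does not serve that purpose.
- The percentages for zero gain restate the zero-gain assumption. The assumed 20% also should not be read as the loss allowance under Sample size, which covers losses and refusals in the whole sample and not exits under this rule.

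The per-protocol analysis does not fill the gap, since children who left for low compliance would ordinarily be outside that set.

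**Conclusion.** The concern holds in a limited form. The only named sensitivity analysis, in its standard form, shares the main method's assumption and would not reveal a departure from it, while the exit rule makes a departure plausible in the exercise arm alone. An overstated intention-to-treat effect is possible but not shown. It requires that children leave under the rule, have no T1 scan and gain less than those who stay, and that the models omit compliance. A reader might take a figure such as 25% as the expected bias. The documents do not support that, because they give neither the share leaving nor the leavers' outcomes. Under the assumptions shown, the overstatement runs from 5% (10% leaving, half the gain kept) to 43% (30% leaving, no gain). The planned use of multiple imputation can stand. This is a worthwhile, inexpensive improvement and not a fatal fault.

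**What to change.** Keep multiple imputation as the main method and include recorded diary compliance in the imputation model. Add to the propensity-score check, or replace it with, at least one analysis that departs from missing at random. Two suitable choices are:

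- control-based imputation for exercise-arm children without a T1 scan; or
- a delta-adjusted (tipping-point) analysis that lowers imputed exercise-arm values in steps until the conclusion changes.

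It would also help to say whether children who leave under the rule are still asked to attend T1.

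The cost is a sentence or two of text and a little more analysis work, with no new data for the analyses themselves. The sensitivity estimate may be less favourable. Control-based imputation is conservative if leavers keep some gain, so it should be reported as a bound beside the main estimate and not as a replacement for it.
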